##### Deteriorating patient database and electronic medical record (eMR)

Patient’s that have a rapid response call activated while an inpatient in a study ward will be identified through existing site rapid response databases. In addition to reviewing the quality of documentation using the audit tool (Supplement 1), these records will be reviewed to identify causal factors associated with the rapid response call and determine if suboptimal inpatient nursing care was a precursor, for example, unreported or delayed reporting (> 30 min) of vital sign abnormalities fulfilling hospital criteria. The instrument (Supplement 1) outlines the variables collected and incorporates the validated Human Factors Classification Framework for patient safety [38], which considers equipment, work environment, staff action and patient factors. To ensure consistent data collection, research nurses assessing clinical documentation and patient deterioration events will complete data collection on a minimum sample of 10 duplicate records to complete inter-rater reliability at commencement. Ongoing audits will maintain data collection consistency.

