##### Hypotheses

The evaluation of the intervention will test the seven hypotheses listed in Table 1.

**Table 1 Tab1:** List of the seven primary hypotheses to be tested throughout the implementation and evaluation of HIRAID® Inpatient

Hypothesis	Implementation of HIRAID® Inpatient will result in a…
H_1_	…20% reduction in rapid response team activation due to preventable patient deterioration
H_2_	…10% reduction in Hospital Acquired Complications (HAC03 and HAC06)
H_3_	…20% reduction in events causing patient harm or near miss
H_4_	…10% improvement in experience of care reported by patient or carer
H_5_	…10% increase in quality of nurse communication and handover
H_6_	…healthcare resource use and cost estimates that will lead to favourable cost-effectiveness estimates
H_7_	…high fidelity (80%) implementation

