#### Study Plan

##### Integration of HIRAID® Inpatient framework into hospital systems

The local electronic and paper-based documentation systems will integrate the HIRAID® Inpatient documentation templates. HIRAID® Inpatient will include a standardised template with fields and prompts for all framework elements. Hospital local factors, such as paper or electronic documentation will inform adaptation practices. Features like the product(s) used (e.g. PowerChart, Cerner electronic medical records (eMR)), automation features, and compatibility with existing tools are included. The documentation templates are designed to streamline assessment documentation, minimise duplication, alleviate administrative burdens, and reduce redundancies for hospital ward nurses. The HIRAID® Inpatient framework will be implemented alongside existing standard nursing care. No concurrent interventions are prohibited during the implementation period; however, any new initiatives or changes to routine care that may influence study outcomes will be documented.

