#### Outcomes

##### Patients with a preventable clinical deterioration (H_1_)

Rate per 1000 admissions of preventable patient deterioration calls (RRT calls) related to nursing assessment and management, observation and monitoring. RRT activation is already recorded in local databases and will be used to identify patients for medical record review, independent assessment and verification of causal factors [38]. Secondary outcome is transfer to a higher level of care (e.g. to Intensive Care Unit) (Table 3).

**Table 3 Tab3:** Summary of HIRAID® Inpatient outcome measure, data collection sources and measurement timepoints

Outcome	Outcome description	Outcome measure	Data analysis	Data source	Control (pre)	Implementation	Intervention (post)
Patient health outcomes							
Outcome 1 (H1)	Nursing-related preventable clinical deterioration	Incidence of clinical deterioration events related to nursing assessment and care	*Descriptive approach, generalised linear model (GLM) approach	Patient deterioration database, eMR records	✓	-	✓
Outcome 2 (H1)	Transfer to higher level care	Incidence of patients transferred to higher level care	*Descriptive approach, GLM approach	Patient deterioration database, eMR records	✓	-	✓
Outcome 3 (H2)	Hospital Acquired Complications (HACs) influenced by nursing care	Incidence of patient days with respiratory complication (HAC03), and/or healthcare-associated infections (HAC06)	*Descriptive approach, GLM approach	Health District data collections, Performance Planning Unit (PPU) database, eMR records	✓	-	✓
Outcome 4 (H2)	HACs influenced by nursing care–health service perspective	Incidence of hospital resource use and costs	*Descriptive approach, GLM approach	Health District data collections, PPU database, eMR records	✓	-	✓
Outcome 5 (H2)	HACs influenced by nursing care	Rate of all other HACs (not HAC03 and HAC06)	*Descriptive approach, GLM approach	Health District data collections, PPU database, eMR records	✓	-	✓
Outcome 6 (H3)	Events that cause patient harm or near miss	Incidence/proportion of adverse patient harm or near miss events	*Descriptive approach, GLM approach	Health District data collections, PPU database, eMR records	✓	-	✓
Patient and carer experience outcomes							

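### H1 status is judged from a patient record that the intervention itself changes, so the classification of calls can shift between conditions, in either direction, with no change in care

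*Protocol article*

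**What the plan says.** Table 1 of the protocol article sets H1 as a "20% reduction in rapid response team activation due to preventable patient deterioration". The H1 paragraph under Outcomes defines the measure as "Rate per 1000 admissions of preventable patient deterioration calls (RRT calls) related to nursing assessment and management, observation and monitoring". It adds that rapid response activations already held in local databases "will be used to identify patients for medical record review, independent assessment and verification of causal factors". The databases find the call, and the record review decides whether it counts.

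The section on the deteriorating patient database and eMR describes that review. Reviewers are to "determine if suboptimal inpatient nursing care was a precursor, for example, unreported or delayed reporting" of vital sign abnormalities meeting hospital criteria, with late meaning more than 30 minutes. The form is in Supplement 1. It uses a human factors classification covering equipment, work environment, staff action and patient factors.

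The intervention acts on the same records:

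- Study Plan, integration into hospital systems: "The local electronic and paper-based documentation systems will integrate the HIRAID® Inpatient documentation templates", and HIRAID Inpatient "will include a standardised template with fields and prompts for all framework elements". The Rationale lists communication and reassessment among those elements.
- Supporting materials: nursing documentation is audited every fortnight during rollout.
- Nursing documentation (H5): documentation quality is an outcome, scored on a sub-sample of the H1 records.

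**The concern.** The source used to classify H1 events changes when the condition changes. Suppose a nurse tells the doctor promptly about an abnormal observation but writes nothing. In the control period the record may read as a failure to report. After rollout the same nurse, acting the same way, completes a communication field and the call may no longer be classed as preventable. The reverse can also happen. Observations charted more often or with clearer times can reveal a delay that the older notes would have hidden, and so add an event.

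H1 is the first-listed hypothesis. If its numerator moves with record-keeping, a fall cannot be read with confidence as fewer preventable deteriorations, and an absent fall cannot be read with confidence as no benefit.

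**Working it through.** The protocol article states no figure on this point that could be reproduced. It gives no baseline H1 rate, and Table 4 is not shown. The check is therefore mainly a comparison of passages.

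**1. Where the classification comes from.** Table 3 lists two sources for the H1 outcome: the patient deterioration database and eMR records. The first identifies calls. The text assigns the judgement on causal factors to record review. It does not say that time-stamped data take precedence over notes.

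**2. Whether the record changes with condition.** It is meant to. Templates and audits arrive with the intervention, and the Rationale reports that HIRAID improved documentation in emergency departments. The H1 records are also the ones scored for quality: "In addition to reviewing the quality of documentation using the audit tool (Supplement 1), these records will be reviewed to identify causal factors" behind the call.

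**3. Whether the stated safeguards reach the problem.**

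- Blinding of those assessing deterioration (Blinding): a blinded reviewer still reads a fuller record in one condition than in the other. A visible HIRAID template could also reveal the condition.
- At least 10 duplicate records at commencement, then ongoing audits: these test agreement between reviewers. Two reviewers can agree fully on an incomplete note.
- Objective assessment and repeated measurement (Methodological considerations and risks): repetition does not remove a shift tied to the condition.

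**4. Why neither size nor sign can be fixed.** Express everything as a share of the calls classed as preventable in the control period, with care unchanged:

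- u = share so classed only because a report was made but not written down;
- r = share of those that the template brings into the record;
- v = additional calls classed as preventable only because fuller charting shows a delay.

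The apparent relative change in H1 is v − u × r. None of the three is in the document, so these inputs are pure assumptions. With u = 0.30 and r = 0.67, u × r = 0.201, and:

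| v | v − u × r | apparent change |
|---|---|---|
| 0 | 0 − 0.201 | −20.1% |
| 0.10 | 0.10 − 0.201 | −10.1% |
| 0.20 | 0.20 − 0.201 | −0.1% |
| 0.30 | 0.30 − 0.201 | +9.9% |

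With u = 0.10 the downward part cannot exceed 10%, even at r = 1. The table shows only that the sign depends on unknown inputs. It is not an estimate for this trial.

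**The case against.** The strongest reply has four parts.

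- **Reporting failure is only an example.** H1 also covers assessment, management, observation and monitoring, and the instrument looks at several causal domains. A missed assessment does not depend on whether a phone call was noted. This stands. A reader might infer that missing documentation of a report by itself makes a call an H1 event; the text does not say so.
- **The form is not shown.** Supplement 1 may already separate undocumented from absent reporting. This also stands. The point rests on the source of the judgement and on the safeguards the article names, not on a claim about what the form lacks.
- **The evidence is wider than nursing notes.** The eligibility section covers charts, progress notes and other documentation of deterioration, and some times may come from charted observations and call logs. This narrows the problem. It does not remove it, since nothing says those sources govern.
- **A partial check exists.** Transfer to higher-level care is a secondary H1 outcome that needs no preventability judgement. This is true, but it is a different event and does not show how far classification has drifted.

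Two stronger readings are tempting. One is that better notes must lower H1 by some calculable part of the 20% target. The documents do not support it: the direction is open, no rates are given, and H5's target, a "10% increase in quality of nurse communication and handover", is not the probability that a report gets written down. The other is that H1 should be redefined as the time from first abnormal vital sign to the rapid response call. The protocol's 30 minutes concerns reporting. A nurse who told the doctor promptly would be counted as late whenever the team was called later.

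**Conclusion.** The concern holds as a risk of differential outcome classification. H1 status is read from a record that the intervention redesigns, and the named safeguards do not address a difference in record content between conditions. The bias can run either way. Its size cannot be estimated from the protocol article.

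The conclusion rests on two assumptions: that reporting failures make up a material part of the calls judged preventable, and that the unseen review form does not already isolate undocumented reporting. If either is wrong, the point shrinks. It does not show that H1 is invalid or that an observed fall would be an artefact. It shows that, as described, readers could not tell how much of a change comes from record-keeping, and that a cheap addition would let them judge.

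**What to change.** Keep the H1 definition and add the following before recruitment opens, scheduled for 1 July 2026:

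1. On the review form, code reporting of the abnormality as documented within 30 minutes, documented after 30 minutes, or not determinable from the record. If Supplement 1 already does this, say so in the text.
2. Report the not-determinable share by condition.
3. Run two sensitivity analyses of H1 in which calls whose status turns on undeterminable reporting are counted first all as preventable, then all as not preventable. With D other preventable calls, N such calls and A admissions, the rates per 1000 are 1000 × (D + N)/A and 1000 × D/A in each condition.
4. Report the all-cause rapid response call rate per 1000 admissions from the same databases beside H1. It does not depend on the preventability judgement, although it may itself change if nurses escalate more readily.

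The cost is one code on an existing form and a few analyses of data already being accessed. One limit remains: these steps show the effect of undocumented reporting directly, but delays exposed by more frequent charting are checked only indirectly, through the all-cause rate.

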##### Hospital data collections

Reports from existing hospital data collections will be accessed. The principal executive at each cluster has confirmed that these data can be provided. Data will be extracted from the relevant financial unit for each ward pre and post implementation to enable economic evaluation of any cost benefits associated with adverse event rates associated with the implementation of HIRAID® Inpatient framework across the sites.

##### Surveys

Surveys will be distributed electronically to nominated emails for patients/carers, and staff emails to all nursing, medical and allied health staff who meet the inclusion criteria. Participants who complete the pre- and post-intervention surveys will be offered a range of $20 vouchers, in accordance with the NSW Classification and Remuneration Guidelines for NSW Government Boards and Committees and as a strategy known to increase response rates.

##### Patient carer experience surveys

To assess patient experience, two instruments will be used (Supplement 2). The AHPEQS [49] is a validated survey that has been developed with input from Australian consumers [40]. The AHPEQS consists of 12 questions related to patient experience. The validated Schmidt’s Perceptions of Nursing Care Survey [50] will be used to measure patient perceptions of nursing care. The survey consists of 15 items on a 5-point Likert scale from strongly disagree (1) to strongly agree (5).

On the day of discharge or within two weeks of discharge from the hospital ward research nurses will make a follow-up call (Supplement 3) to complete the survey. If the time is not convenient, they will arrange an alternate time and day for survey completion as soon as practical. While the likelihood of the patient being deceased is low, as part of the preliminary phone call to carers, the well-being of the patient will be ascertained using sensitive and considerate language (outlined in the interview script). The research nurse will also access the patient’s medical record to ascertain if the patient has been readmitted since discharge and is an inpatient again, or deceased. If deceased, they will not call. The same approach will be used if any subsequent calls are required to complete the survey (Supplement 3).

##### Nursing staff surveys

For the nursing staff, a survey will be distributed to collect the following:Nurse characteristics (control and intervention). A short survey will collect data on nurses’ position, experience and expertise. Gender will not be collected, as we do not plan to target male, female, or non-binary staff any differently in our implementation strategy [51].Nurse confidence (control and intervention). Confidence in patient assessment and communication will be measured using a validated survey for use in the Australian setting [31]. The scale consists of 14 items and nurses indicate their level of confidence for each item on an 11-point Likert scale ranging from no confidence (0) to complete confidence.Nurse experience with communication (control and intervention). We will measure nurse experience with registered nurse (RN) communication and quality of information received during handover, using a previously validated instrument [31]. This instrument consists of 8 items on a 11-point Likert scale, five yes/no questions and a free text box for written responses.Nurse perception of practice environment (control only). We will measure nurses’ perception of the practice environment using the validated *Practice Environment Scale of the Nursing Work Index (PES-NWI).* This will determine if the proposed implementation, use and effect of HIRAID® Inpatient varies due to organisational and other factors that influence a nurse’s ability to practice skilfully and deliver high quality care. The PES-NWI consists of 28 items and nurses indicate their agreement on a 4-point Likert scale ranging from strongly disagree (1) to strongly agree (4).HIRAID® Inpatient feedback and evaluation (intervention only). This brief survey will measure nurses’ overall perception of HIRAID® Inpatient, its effectiveness and the implementation process developed in Phase 2 of the study and used in the rollout of the framework across the local health district (Phase 3). As such, the exact number of items is not yet known. Responses will follow a yes/no format or a 5-point Likert scale measuring frequency (1—never to 5—always), with opportunity to provide free text explanations. Findings will inform a future toolkit, focusing on implementation strategies, organisational support, uptake of protocols, utility and sustainability.

Data from these surveys will have multiple purposes. Responses to the practice environment (PES-NWI) and behavioural diagnostic instruments (control only) will inform the implementation strategies of the HIRAID® Inpatient intervention at the respective ward. The final feedback and evaluation instrument will collect nursing staff feedback on intervention implementation, assessing rollout strategies to inform the development of a future toolkit.

##### Medical and allied health staff survey

Medical and allied health staff satisfaction with nurse communication (control and intervention). Staff satisfaction with RN communication and quality of information received during handover, using a previously validated eight-item, 11-point Likert scale, plus five yes/no questions instrument [31]. The opinion of permanently employed medical and allied health staff is sought as a component of HIRAID® Inpatient communication. A unique identifier will be generated by responders to enable post-intervention matching. The survey will be distributed electronically and used to inform H5 (improved quality of nursing communication and handover).

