##### Education and training of nursing staff

All nursing staff will participate in education sessions designed to teach the theory and application of HIRAID® Inpatient, using a pedagogically informed approach [32]. The education programme will be co-developed with experts from the participating organisations and will incorporate principles of constructive alignment [33–35], backwards design [36] and scaffolded learning [37] to ensure coherence between learning outcomes, resources and activities.

The education programme will consist of two different training sessions, the instructor and the provider training. The HIRAID® Inpatient Instructor training will be designed to equip healthcare professionals with the skills to teach and implement the framework, and focuses on developing teaching strategies, and applying HIRAID® to a clinical setting. CNCs/CNEs and senior nurses at each site will receive HIRAID® Inpatient Instructor training and will lead delivery of HIRAID® Inpatient Provider courses for all RNs and ENs from participating wards using a train-the-trainer model. Senior RNs will undergo Instructor training to independently deliver HIRAID® Inpatient training, supporting long-term sustainability. The HIRAID® Provider training will focus on equipping clinicians with the skills to use the framework. Completion of the HIRAID® Inpatient Provider Course will be mandatory for new nursing staff and will be embedded into orientation and onboarding programmes through the established instructor network.

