#### Statistical methods

##### HIRAID® effectiveness/clinical outcomes

Survey and health record data collected for implementation evaluation will be analysed using descriptive statistics to assess fidelity levels and feedback from study sites. Descriptive statistics will be calculated using the chi-square test for categorical variables, and the *T*-test (normally distributed data) or the Mann-Whitney *U* test (non-normally distributed data) for continuous variables. All analyses will follow the intention-to-treat principle, with all clusters evaluated according to their original group allocation, regardless of adherence or protocol deviations. Comparisons within and across clusters will be conducted using the generalised linear mixed model (GLMM) approach, applying appropriate link functions tailored to each outcome variable. For binary outcome measures, a GLMM with a binary logistic link function will be used, while for count outcome measures, GLMMs with Poisson or negative binomial link functions will be applied. The model will account for the random effect of the cluster and will adjust for relevant confounders, identified in the descriptive analyses, as fixed effects. SPSS V28™ (IBM Corp., Armonk, NY, USA) will be used and the alpha set to < 0.05 [18].

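### Staff-survey Outcomes 9 and 10 (H5): a respondent code is collected for matching, but no named analysis uses it, and no code is described for nurses

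*Protocol article*

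**What the plan says.** All references are to the protocol article.

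- **Medical and allied health staff survey:** handover satisfaction is measured in control and intervention periods, and "A unique identifier will be generated by responders to enable post-intervention matching".
- **Surveys:** $20 vouchers are offered to participants who complete the pre- and post-intervention surveys, so repeat response is expected.
- **Nursing staff surveys:** nurses receive a handover instrument of the same format and citation (eight items on an 11-point scale plus five yes/no questions). They also receive the confidence scale: "Confidence in patient assessment and communication will be measured using a validated survey for use in the Australian setting". Both run in control and intervention periods. Nurse characteristics are recorded in both as well: "A short survey will collect data on nurses’ position, experience and expertise". No respondent code is mentioned.
- **Education and training of nursing staff:** staff turnover is foreseen, since "Completion of the HIRAID® Inpatient Provider Course will be mandatory for new nursing staff".
- **Table 3:** Outcome 9 (handover) is assigned multiple linear, linear and logistic regression, and Outcome 10 (confidence) multiple linear regression.
- **Statistical methods, HIRAID® effectiveness/clinical outcomes:** t-test or Mann-Whitney for continuous variables, then a generalised linear mixed model, of which it is said that "The model will account for the random effect of the cluster and will adjust for relevant confounders". No paired test and no respondent effect is named.
- **Table 1:** the H5 target is a "10% increase in quality of nurse communication and handover".

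**The concern.** The plan collects a link for a stated purpose and then names analyses that cannot serve that purpose. If the same people answer before and after, their two scores are positively correlated. A before-after difference then has a smaller variance than a model assuming independence reports, so intervals are too wide, tests are conservative and power is lost.

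The nurse surveys raise a second issue. The two waves are separated by at least the three-month transition, with control and exposure periods of 3 to 12 months, so some nurses will leave and others join. Without a person-level link, a change in who answers cannot be separated from a change in the people who answered twice.

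The timing matters. A respondent effect can be added to a model later, but a code that was never asked for cannot be recovered. Recruitment is scheduled to start on 1 July 2026.

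**Working it through.** **Inputs.** The documents give no standard deviation, baseline mean, turnover rate or within-person correlation, and the H5 sample size sits in Table 4, which is not shown. There is therefore no stated figure to reproduce, and everything below is sensitivity arithmetic on assumed values. Let m be the share of respondents who answer both waves and ρ the within-person correlation. The waves are of equal size n with common variance σ². The contrast is a simple before-after difference that ignores the stepped-wedge structure of four clusters.

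**1. Reported against true standard error when the link is ignored.**

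- Variance reported under independence: 2σ²/n.
- True variance of the same unlinked difference: (2σ²/n)(1 − mρ).
- Ratio of reported to true standard error: 1/√(1 − mρ).
- With m = 0.6 and ρ = 0.5: 1/√0.70 = 1.195.
- Actual two-sided error at nominal 5%: the critical value becomes 1.96 × 1.195 = 2.34, giving about 1.9%.
- Over m = 0.5 to 1 and ρ = 0.3 to 0.7 the ratio runs from 1.09 to 1.83.

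**2. True precision gained by using the link.**

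- Generalised least squares information, relative to two independent samples: m/(1 − ρ) + (1 − m).
- Variance of the linked estimate, in units of 2σ²/n, is its inverse. The fair comparator is 1 − mρ, the true variance of the unlinked estimate.

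| ρ (m = 0.6) | Relative information | Linked variance | Unlinked true variance | True SE ratio | Fall in true SE |
|---|---|---|---|---|---|
| 0.3 | 0.6/0.7 + 0.4 = 1.257 | 0.795 | 0.82 | √(0.795/0.82) = 0.985 | 1.5% |
| 0.5 | 0.6/0.5 + 0.4 = 1.600 | 0.625 | 0.70 | √(0.625/0.70) = 0.945 | 5.5% |
| 0.7 | 0.6/0.3 + 0.4 = 2.400 | 0.417 | 0.58 | √(0.417/0.58) = 0.848 | 15% |

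**3. Possible shift from nurse turnover.**

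- Shift = t × g, where t is the share of later respondents who replaced leavers and g is the joiner-minus-leaver gap as a percentage of the baseline mean. The 10% target is read as relative to that mean.
- t = 20%, g = +10%: 0.20 × 10 = 2% of the mean, a fifth of the target.
- t = 30%, g = ±15%: 0.30 × 15 = 4.5% of the mean in either direction, or ±45% of the target.
- g = 0: no shift.

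**4. Does a respondent random effect remove that shift?** Suppose 20% leave, score 1 point below the rest on the 0–10 scale and are replaced by nurses who score like the stayers.

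- Unlinked bias: 0.20 × 1 = 0.20 points.
- With linkage at ρ = 0.5, stayers carry weight 0.8/0.5 = 1.6 and the leaver-joiner comparison weight 0.2, so the bias is 0.2 × 1/(1.6 + 0.2) = 0.11 points.
- Among stayers only, this source of bias is zero.

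**The case against.** Several objections are sound and limit the point.

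- **Silence is not absence.** The article condenses a fuller protocol, which may give nurses a code. Surveys go to staff emails, and vouchers are tied to completing both waves, so some linkage may exist. A reader might infer that nurses definitely have no code; the text shows only that none is described.
- **Unlinked surveys can be legitimate.** Surveying whoever is in post in each period is an accepted design, and H5 does not say that it concerns change in the same individuals. A reader might infer that turnover will be counted as an intervention effect. The documents do not support that. Bias needs leavers and joiners to differ beyond position, experience and expertise, which are collected in both conditions and can be adjusted for. Its size and sign are unknown.
- **The precision gain is easily overstated.** Setting the linked variance against two fully independent samples gives √(1/1.6) = 0.79, an apparent 21% fall. Most of that is correction of a standard error that was reported too large. The true gain at the same inputs is 5.5%.
- **The unpaired tests are introduced as descriptive.** The t-test and Mann-Whitney may not be the main effect analysis. This does not rescue the plan, because the regressions in Table 3 and the cluster-only mixed model do not use the link either.

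What remains is a mismatch within the article: matching is a stated purpose for one staff group, repeat answers are expected, and no named analysis uses the match.

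**Conclusion.** The point holds in a limited form, for Outcomes 9 and 10 only. As written, the analysis treats repeat answers from one person as independent. In a simple before-after contrast this overstates the standard error by a factor of about 1.2 at m = 0.6 and ρ = 0.5. The error is conservative and costs power; it does not create false positives. Using the link would also lower the true standard error by about 5.5% (1.5% at ρ = 0.3, 15% at ρ = 0.7). All these inputs are assumed, and the figures do not model the stepped-wedge design.

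For nurses the conclusion is conditional. If the full protocol provides no code, stayers, leavers and joiners cannot be distinguished, and turnover could shift the contrasts either way, or not at all. Documentation quality (Outcome 11), which the outcomes section scores on a sub-sample of patient records, does not depend on linking survey respondents.

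**What to change.** 1. Before control data collection starts, put the same respondent-generated code in the nurse surveys as in the medical and allied health survey. If the full protocol already has one, say so.
2. For Outcomes 9 and 10, add a respondent random effect to the planned mixed model. Keep all respondents and adjust for the nurse position, experience and expertise already collected.
3. Report within-person change among stayers as a sensitivity analysis. It is needed because the random effect reduces turnover bias without removing it (0.20 to 0.11 points in the example above).

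The cost is one question in an electronic survey and one extra model term. Some codes will not match, and those respondents would be analysed as unlinked. Nurses must be assured that the code does not identify them.
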